## Abstract

**Background:**

Mid-portion Achilles tendinopathy is a common musculoskeletal condition characterised by degeneration of the Achilles tendon, which causes pain and disability. Multiple non-surgical treatments have been advocated for this condition including calf muscle eccentric exercise and in-shoe heel lifts. Although adherence is challenging, there is evidence to suggest that calf muscle eccentric exercise is effective in decreasing pain and improving function in people with Achilles tendinopathy. Heel lifts reduce ankle joint dorsiflexion and Achilles tendon strain, however their efficacy in the management of Achilles tendinopathy is unclear. This article describes the design of a parallel-group randomised trial comparing the efficacy of heel lifts to calf muscle eccentric exercise for Achilles tendinopathy.

**Methods:**

Ninety-two participants with Achilles tendinopathy will be randomised to one of two groups: (i) a heel lift group that will receive pre-fabricated 12 mm in-shoe heel lifts (Clearly Adjustable®), or (ii) an exercise group that will be advised to carry out a calf muscle eccentric exercise program (twice a day, 7 days a week, for 12 weeks). Outcome measures will be obtained at baseline, 2, 6 and 12 weeks; the primary endpoint for assessing efficacy being 12 weeks. The primary outcome measure will be the total score of the Victorian Institute of Sport Assessment – Achilles (VISA–A) questionnaire. Secondary outcome measures will include thickness and integrity of the Achilles tendon (using ultrasound tissue characterisation [UTC]), participant perception of treatment effect on pain and function (using the 7-point Patient Global Impression of Change scale), severity of pain at the Achilles tendon (using a 100 mm visual analogue scale) in the previous week, health status (using the EuroQol-5D-5L™ questionnaire), physical activity levels (using the 7-day Recall Physical Activity Questionnaire) and calf muscle function (using the standing heel rise test). Data will be analysed using the intention to treat principle.

**Discussion:**

The HEALTHY trial (Heel lifts versus calf muscle eccentric Exercise for AchiLles TendinopatHY) is the first randomised trial to compare the efficacy of heel lifts to calf muscle eccentric exercise in reducing pain and improving function in people with Achilles tendinopathy. A pragmatically designed trial was developed to ensure that if the interventions are found to be effective, the findings can be readily implemented in clinical practice.

**Trial registration:**

Australian New Zealand Clinical Trials Registry: ACTRN12617001225303. Registered on August 22nd, 2017.

**Electronic supplementary material:**

The online version of this article (10.1186/s13047-019-0325-2) contains supplementary material, which is available to authorized users.

## Background

Mid-portion Achilles tendinopathy is a common overuse soft tissue injury causing pain and stiffness with incidence rates reported to be 1.85 per 1000 people in the general population [1]. The majority of people with Achilles tendinopathy are active and involved in recreational or competitive sport [2]. Achilles tendinopathy is common in running populations with prevalence rates up to 9.5% [3] and a lifetime risk of 52% for top level (elite) runners [2]. However, the condition also affects inactive populations with 1 in 3 people with the condition leading a sedentary lifestyle [1]. Increased age is a contributing factor for the condition as it is reported most frequently by people aged between 40 and 59 years [4]. Obesity has also been associated with the condition [1]. People with Achilles tendinopathy typically report symptoms of pain and stiffness upon weight bearing after prolonged rest [5] and at the start of physical activity, which reduces as the activity continues [5]. These symptoms lead to impaired performance [6]. In more severe cases, pain and disability can be persistent with functional activities such as walking [7].

Numerous interventions have been advocated for the initial management of Achilles tendinopathy, including: exercise [8, 9], stretching [10], neuromuscular re-education [11], activity modification [12], patient counselling [12], in-shoe heel lifts [13], night splints [14], taping [15], low-level laser therapy [16], iontophoresis [17], dry needling [18], corticosteroids [19], and extracorporeal shockwave therapy [20]. However, the evidence supporting these interventions for the management of Achilles tendinopathy is equivocal [21]. When non-surgical interventions are ineffective, surgical management may be required, which is carried out in approximately 30% of people with the condition [6].

Exercise programs remain the most widely researched intervention for the management of Achilles tendinopathy [21, 22]. Multiple exercise programs have been described that include eccentric, concentric, isometric, and/or isokinetic contractions. Further, the proposed frequency, load, and speed of exercise programs have varied, and optimum exercise protocols are yet to be established [23]. For more than two decades, the eccentric calf muscle exercise protocol proposed by Alfredson [24] has been most frequently reported in literature and widely used by practitioners. The program involves three sets of 15 repetitions performed twice daily for 12 weeks with external resistance (as a percentage of body weight) added in the latter stages of the program with the aim to improve the tendon’s ability to withstand load. Although the program is inexpensive and evidence from systematic reviews and randomised trials have shown the eccentric exercise program decreases pain and improves function in people with Achilles tendinopathy [8, 25], the program is not without its limitations. The mechanism for its efficacy remains unclear and the program is time consuming. This may explain the variability in adherence [25–27], with the intervention reported to be unsuccessful in up to 44% of people with Achilles tendinopathy [20, 28]. A longer duration of symptoms, greater severity of the condition [28], and inactivity [28] have all been found to reduce the effectiveness of this intervention.

In-shoe heel lifts are another intervention advocated for the management of Achilles tendinopathy [29]. Heel lifts are inexpensive shoe inserts designed to place the ankle into a more plantarflexed position [30] and reduce Achilles tendon strain. Experimental studies have supported the use of heel lifts, showing reductions in ankle joint dorsiflexion during running [31], as well as reductions in Achilles tendon strain [32, 33], gastrocnemius activity [34], and peak force of posterior leg muscles [35] during walking. Despite this, there are only two low quality studies that have evaluated the efficacy of heel lifts for the management of Achilles tendinopathy. In a randomised trial, Lowdon and colleagues [36] evaluated the efficacy of rubber 15 mm heel lifts (Sorbothane® heel pads [*n* = 11], Molefoam heel pads [*n* = 10], and no heel pads [*n* = 12]) for “sports-induced Achilles tendinitis” in 33 participants aged 11 to 51 years. Participants who were randomised to receive heel lifts reported improvements in pain, swelling and tenderness associated with Achilles tendinopathy at two months, however there were no between-group comparisons. In addition, a case series [29] evaluated the benefits of heel lifts for “Achilles tendonitis” in 14 participants. At three months, the majority (11/14) of participants reported returning to activity pain free. Although this was a favourable outcome, this study had a small sample size, no control group, and the heel lift height was unspecified. Clearly, there is insufficient evidence to demonstrate the effectiveness of heel lifts in the management of Achilles tendinopathy.

Given the limitations of the available evidence, the aim of this randomised trial is to evaluate the efficacy of heel lifts versus calf muscle eccentric exercise for Achilles tendinopathy.

## Methods

This trial protocol has been reported in accordance with the Standard Protocol Items: Recommendations for Interventional Trials (SPIRIT) guidelines [37]. The SPIRIT checklist is included in an additional file [see Additional file 1].

### Design

The HEALTHY study (Heel lifts versus calf muscle eccentric Exercise for AchiLles TendinopatHY) is a parallel-group randomised superiority trial (Fig. 1) with a 12-week follow up. Participants will be randomised to receive one of two interventions: (i) Clearly Adjustable® pre-fabricated in-shoe heel lifts, or (ii) a calf muscle eccentric exercise program. All participants will receive an intervention, therefore there are no ethical concerns of not treating participants experiencing pain.

**Fig. 1 Fig1:**
[figure not shown]
Study protocol

Due to the nature of the intervention, research staff administering the interventions (i.e. the therapists) and assessing outcomes (i.e. the assessors) will not be blinded to group allocation. Similarly, it is not possible to blind the participants. However, research staff entering and analysing data will be blinded.

Assessments will occur at baseline (initial), 2, 6 and 12 weeks. Assessments will be performed at the La Trobe University Health Sciences Clinic, Melbourne (Victoria, Australia) with the exception of the 6 week assessment (postal questionnaire).

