#### Musculoskeletal ultrasound assessment

Participants will undergo musculoskeletal ultrasound using ultrasound tissue characterisation (UTC) imaging of the Achilles tendon by a registered podiatrist ([name]) at baseline (initial) and 12 weeks. An algorithm will be used to classify the Achilles tendon as normal or pathological (Fig. 2). Participants who display either local thickening [42], irregular fibre orientation, or irregular tendon structure with hypoechoic areas within the mid-portion of the Achilles tendon [52] will be diagnosed with Achilles tendinopathy [20]. Certain features have been shown to concomitantly exist in those with Achilles tendinopathy, and may also exist in asymptomatic individuals [43]. Therefore, participants will not be excluded if they have aforementioned sonographic features accompanied by fluid in the retrocalcaneal bursae (up to 4.0 mm), focal calcifications, paratenon thickening (considered to be present if the paratenon measures more than 2.0 mm in thickness) [43] or calcaneal cortical anomalies (such as spurring).

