### Interventions

#### Random allocation and concealment

Participants will be randomised to one of two groups: (i) a heel lift group (pre-fabricated heel lifts [Clearly Adjustable®]), or (ii) an exercise group (calf muscle eccentric exercise program). To ensure allocation concealment, a cloud-based randomisation service provided by Griffith University, Queensland, Australia, will be used. The random allocation sequence will be generated with a 1:1 allocation ratio using permuted blocks of random sizes.

Interventions will be administered by [name], a registered podiatrist with five years clinical experience. Prior to the trial, [name] will be mentored and undergo training sessions by the senior members of the research team who have extensive expertise in the assessment and management of musculoskeletal disorders including Achilles tendinopathy.

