#### Secondary outcome measures

Secondary outcome measures include: (i) thickness and integrity of the Achilles tendon, (ii) participant perception of treatment effect, (iii) severity of pain, (iv) health status, (v) level of physical activity in the previous week and (vi) calf muscle function. Secondary outcome measures are described in more detail below.(i)Thickness and integrity of the Achilles tendon: ultrasound tissue characterisation (UTC) will be used to visualise the Achilles tendon structure (including thickness) and assess tendon integrity. Participants will be positioned prone, with feet overhanging the examination table and in a neutral position to examine the tendon and paratendinous structures in the transverse and longitudinal planes [43]. A high resolution probe positioned in the UTC tracking device will move automatically along the long axis of the Achilles tendon. The UTC device will be positioned on the posterior surface of the Achilles tendon parallel to the tendon’s long axis, at the Achilles insertion (proximal aspect of the calcaneus). Scanning will be conducted proximal to distal. The maximum anterior-posterior tendon thickness will be measured using electronic callipers [43, 53].

The tendon structure of each participant will be quantified by percentage of the four echo-types as described by Van Shie et al. [57]:Echo-type I: intact, continuous and aligned fibres and fasciuli;Echo-type II: less continuous and/or more wavy fibres and fasciuli;Echo-type III: mainly fibrillary matrix;Echo-type IV: complete disintegration, with tendon tissue replacement by an amorphous matrix and fluid.

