To quantify tendon structure, contours will be manually placed around the Achilles tendon in the transverse view at regular intervals along the length of the Achilles tendon (disappearance of the calcaneus to the musculotendinous junction) [44]. The UTC software (UTC2010, UTC Imaging) automatically interpolates between the contours to create a 3-D volume where proportions of each echo type are calculated. The percentage of echo type I + II (structure-related) and echo type III and IV (non-structure related) will be then be calculated. The percentage of normal tendon (i.e. echo types I and II) will then be determined from this data [57].(ii)Participant perception of the treatment effect: the participant’s perception of treatment effect will be measured separately for pain and function using the Patient Global Impression of Change (PGIC) questionnaire [58]. The scale includes the following questions for participants: ‘Compared to how you were before starting this trial, how is your pain in your Achilles tendon?’, and ‘Compared to how you were before starting this trial, how would you rate your ability to perform physical activities (such as walking, dancing, running, gardening, housework)?’. Each question will have the following responses ‘very much improved’, ‘much improved’, ‘minimally improved’, ‘no change’, ‘minimally worse’, ‘much worse’, or ‘very much worse’. The responses will then be dichotomised according to ‘treatment effectiveness’ where ‘treatment effectiveness’ is defined as ‘much improved’ or ‘very much improved’ [59].(iii)The severity of pain: the severity (intensity) of pain will be measured using a 100 mm VAS, where participants will be asked to, ‘Mark on the line the severity of pain you have experienced in your Achilles tendon when it has been at its worst, over the past week’. Zero (0) implies no pain and one hundred (100) implies the worst pain imaginable [58].(iv)Health status: EuroQol (EuroQol 5D-5 L®), a standardised questionnaire for describing health-related quality of life, will be used to measure health status [60]. This measurement tool consists of five questions addressing mobility, self-care, usual activities, pain/discomfort, and anxiety/depression. The participant will also rate their overall health state from 0 (worst health state imaginable) to 100 (best imaginable health state) using a VAS.(v)Level of physical activity in the previous week: the level of physical activity in the previous week will be evaluated using the 7-day Recall Physical Activity Questionnaire, a valid and reliable tool [61]. This questionnaire has been used previously as an outcome measure in clinical trials of interventions for lower limb musculoskeletal pathologies including Achilles tendinopathy [25, 59].(vi)Calf muscle function: calf muscle function will be measured at baseline and at 12 weeks using the standing heel rise test [62]. This test involves participants using their fingertips lightly placed on a wall for balance, whilst minimising postural sway, standing on their affected side and then repetitively raising onto their toes (moving the ankle into plantarflexion) until fatigue. This test will be performed to the sound of a metronome (one heel rise every 2 s with a metronome set at 60 beats per minute). The maximum number is then recorded. This test has been previously used and shown to have adequate reliability (ICC = 0.61 to 0.98) in both healthy participants [63] and participants with Achilles tendinopathy [64, 65]

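### Outcome assessors are left unblinded with no exception for UTC, although the reason given does not apply to reading recorded scans; the 12-week reading of this secondary outcome is open to avoidable reader bias

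*Protocol article*

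**What the plan says.** The Design section of the protocol article gives one blinding rule for everyone who assesses outcomes, with the nature of the intervention as its reason: "research staff administering the interventions (i.e. the therapists) and assessing outcomes (i.e. the assessors) will not be blinded to group allocation". No outcome is excepted. The same paragraph then adds "However, research staff entering and analysing data will be blinded".

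The section on secondary outcome measures lists tendon structure first: "Secondary outcome measures include: (i) thickness and integrity of the Achilles tendon". Both parts are measured by UTC, at baseline and 12 weeks. The probe travels along the tendon automatically. The reading that follows is manual for integrity: "contours will be manually placed around the Achilles tendon in the transverse view at regular intervals". Software then interpolates between the contours to build a volume and computes the share of each echo-type. For thickness, "The maximum anterior-posterior tendon thickness will be measured using electronic callipers"; whether this is done live or on stored images is not stated.

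The section on musculoskeletal ultrasound assessment describes "ultrasound tissue characterisation (UTC) imaging of the Achilles tendon by a registered podiatrist". No section says who places the contours, or that scans are coded before they are read.

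**The concern.** The stated reason explains why participants and therapists cannot be blinded, and why a live test such as the heel rise is hard to blind. It does not explain unblinded reading of a recorded scan, which shows tendon and carries no trace of a heel lift or an exercise programme.

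The reading step is also where judgement enters. Contours decide which tissue counts towards the echo-type percentages, and calliper placement decides the maximum thickness. A reader who knows the arm can move either result without intending to.

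The other outcomes offer little scope for protection. VISA-A, global impression of change, pain, health status and physical activity are reported by participants who know their allocation, and the heel rise test is performed live until fatigue. UTC is therefore the outcome most easily shielded from expectation. The Discussion counts structural integrity among the clinically relevant measures the trial is meant to capture.

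**Working it through.** **1. Does the stated reason reach each step of UTC?**

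- Acquisition: the probe moves automatically, so the operator has limited influence, although the operator does meet the participant.
- Contouring: manual, on image data from which software then builds a volume. The participant need not be present and the intervention is not visible. The reason does not apply.
- Thickness: electronic callipers placed by an operator. If this is done on stored images, the reason does not apply. If it is done live, it may. The article does not say which.

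**2. Which readings are exposed to knowledge of arm?**

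- Baseline: the Outcome measures section places baseline measurement before randomisation, so there is no arm to know.
- 12 weeks: allocation is known to assessors under the Design section. This is the exposed reading.

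The Statistical analysis section compares continuous outcomes at 12 weeks by ANCOVA adjusted for baseline. An arm-related shift in the 12-week reading passes straight into the adjusted group difference. Blinding the data analyst cannot remove it, because it is already in the data.

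**3. The plan's own sample size.** Inputs from the Sample size section: difference 10, SD 16.9, alpha 0.05, power 80%, 1:1 allocation.

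- Standardised effect = 10 / 16.9 = 0.59.
- A two-sided two-sample t-test needs 45.8 per group, so 46 per group and 92 in total. Power at 46 per group is 80.2%.

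The stated 92 reproduces. It rests on VISA-A, and blind reading of scans does not change it. Only the 46 per arm is carried forward.

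**4. Illustration of sensitivity.** Assume no true difference and a systematic reader shift of s SD between arms.

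- Standard error of the group difference, in SD units = √(2/46), so the shift moves the test statistic by s × √(46/2) = s × √23 = s × 4.796.
- False-positive rate = P(|Z + 4.796s| > 1.96).

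Results:

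- s = 0.1: shift 0.480; P(Z > 1.480) + P(Z < −2.440) = 0.069 + 0.007 = 0.077.
- s = 0.2: shift 0.959; P(Z > 1.001) + P(Z < −2.919) = 0.158 + 0.002 = 0.160.
- s = 0.3: shift 1.439; P(Z > 0.521) + P(Z < −3.399) = 0.301 + 0.000 = 0.301.

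The values of s are assumptions. The article gives no reader-bias, reader-reliability or SD figure for UTC.

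**The case against.** The strongest reply is that the Design section may already answer the point. It blinds staff who analyse data, and contouring is described as a software-based quantification step separate from scanning, so it could be meant as data analysis. That reading is possible but not stated. Measuring an outcome is ordinarily outcome assessment, which the same paragraph declares unblinded. If blinded contouring was intended, one sentence settles the matter.

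It can also be said that a condensed article leaves imaging procedure to the full protocol. That is fair for the missing detail of who reads the scans and when. It does not cover the blanket unblinded statement, which the article itself makes and justifies with a reason that does not fit this outcome.

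Several stronger readings are tempting but unsupported:

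- A reader might infer that the article says the person reading the scans knows both arm and visit. It does not. It names no reader, and the blinding statement concerns allocation only. Knowing the visit alone would act on both arms alike and would not by itself bias the comparison between them.
- A reader might infer that the scanner is also the therapist, since the therapist is "a registered podiatrist with five years clinical experience" and the scanner is a podiatrist too. Names are removed, so this cannot be established.
- A reader might infer that thickness can certainly be read blind. That depends on whether callipers are placed on stored images.
- A reader might take 7.7% to 30% as the trial's actual error rate. The calculation would apply to any continuous outcome with 46 per arm. Both groups receive active treatment, and nothing in the article indicates the direction or likelihood of a shift.

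**Conclusion.** The point holds in limited form. The blanket unblinding of assessors rests on a reason that does not extend to reading recorded UTC scans. Unless contouring was meant to fall under blinded data analysis, the 12-week reading of one secondary outcome out of six is exposed to arm-related reader bias that could be avoided.

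The size of that bias cannot be estimated from the article. The error-rate figures show only that small systematic shifts would matter at this sample size. The primary outcome, its analysis, the sample size and the main efficacy conclusion are untouched.

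The conclusion assumes that UTC data are stored in a form that can be coded. The contour-and-interpolate workflow suggests this, but the article does not say it. The change is worth making because it costs little, not because bias has been shown.

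**What to change.** - Have existing staff other than the reader replace identifiers and visit labels on the stored baseline and 12-week UTC files with random codes.
- Have the existing reader place contours on the coded files in random order, masked to arm and preferably to visit. Measure thickness in the same way where it can be taken from stored images, and state where it cannot.
- Leave the live baseline scan for eligibility as it is, since it precedes randomisation.
- In the Design section, limit the unblinded statement to live assessments and say that UTC reading is masked. If it was already meant to be covered by blinded data analysis, say so explicitly.

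The cost is some file-coding time and a short delay in reading, with no extra reader, scan or visit. Recruitment began in August 2017, but scans already taken can be re-read in this way if the files were kept. Masking may be imperfect if the reader also acquired the scans and recognises them, and the report should say so if that applies.
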